### Plans to promote participant retention and complete follow-up {18b}

Patients will receive extensive information about the study setup, and the importance of completion of the treatment and the follow-up assessments will be stressed. With respect to psychotherapy, whenever a session is missed, the therapist will contact the patient to re-schedule the session and to identify the reasons for non-attendance to prevent missing future sessions. Patients are allowed to abandon the study at any time. The trial coordinators will inquire about the reasons for withdrawal while respecting their right to do so. In addition, they will be encouraged to complete the follow-up questionnaires. This will be important to the intention-to-treat analyses in an attempt to maximize the number of participants in each study arm. All patients will be reminded throughout the study to fill out the questionnaires by individualized emails as well as by therapists and outcome assessors. Throughout the follow-up period, the trial coordinator will check the responses and, if necessary, contact the patients for completion of their follow-up.

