The RGT aims to explore the constructions with which a person represents the interpersonal world in her or his own terms, and it is administered in a semi-structured, face-to-face interview. First, 10 to 20 elements (self now, significant family members and friends, and ideal self) are obtained. Then, the constructs (bipolar dimensions of meaning) the person uses to categorize them are elicited using similarity and difference questions. Note here that the addition of the Ideal Self element (“how I would like to be”) allows the therapist to grasp the person’s goals as well. Then, these elements and constructs provided by the interviewee are entered into a blank grid form to rate each element (self, others, and ideal self) according to the elicited constructs using a 7-point scale, thus creating a data matrix that reflects the construct usage of respondents in their interpersonal world. Multivariate statistical analyses of this matrix reveal the patterns of relationships among constructs and the position of self and others in the meaning system of the individuals being assessed, which can be plotted in a two-dimensional space. Also, Euclidian distances and correlations provide a series of psychological indices (e.g., self-ideal discrepancy) indicating structural characteristics of that system. As reflected in the literature, these analyses have allowed researchers and professionals a detailed and personalized understanding of patients’ personal views of themselves and others, which has been used to target specific psychotherapeutic interventions using case formulation [32, 33].

The three treatment modalities of the study will be applied by psychologists with specific clinical experience and training (master’s level or higher) in the therapy modality assigned. Senior therapists with more than 15 years of experience will conduct specialized training and weekly supervision sessions with the therapists. Indeed, to control for researcher allegiance and to promote high treatment quality in the three arms, the research team involved in the study included senior members with extensive experience in each of the treatment conditions being tested (see the “Authors’ information” section). The treatment will be provided in the health centers in which participants are being recruited.

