## Assignment of interventions: blinding

### Who will be blinded {17a}

Researchers, patients, and therapists will not be blinded since this is impossible due to the major difference between the groups (use of virtual reality in PCT-VR). Moreover, therapists and (senior) researchers will need to follow a manual related to the corresponding arm of the study. However, blinding to study hypotheses will be fostered by explaining to all patients and therapists that the study objective is to assess the efficacy of psychotherapy for young adults, regardless of the type of treatment. On the other hand, researchers conducting outcome assessments will be blind to treatment allocation.

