## Data collection and management

### Plans for assessment and collection of outcomes {18a}

All data from questionnaires will be gathered using an automatized system (e.g., Qualtrics™), even if participants are physically accompanied by their therapist or evaluators when completing the forms. To ensure data collection in every stage (baseline, therapy monitoring, and follow-ups), a number of quality control procedures will be used, such as providing participants with warnings whenever a question has been left blank to minimize the frequency of missing answers, notifying the research coordinator indicating that a participant is not eligible (e.g., the score in the BDI-II is above 28), and warning the research team if a patient is at risk (e.g., suicidal ideation) or a participant has not completed the questionnaire.

Screening interviews will be conducted in synchronous videoconference settings by psychology graduates specifically trained in the MINI by researchers of the team. Interviewers will enter data in the data system right after the interview whereas participants will be emailed individualized links to complete baseline questionnaires (BDI-II, CORE-OM, and DASS-21). All diagnoses will be supervised by the trial coordinator to ensure validity and homogeneity throughout the recruitment process. Then, to monitor the psychotherapy process, participants will also be emailed individualized links to complete the CORE-SFB just before each session, and the SRS 3.0 for the therapeutic alliance at the end. The post-treatment assessment consists of all the baseline measures, including the MINI interview which will be performed, whenever possible, by the same evaluators who carried out the baseline interview and again supervised by the trial coordinator. In addition to these instruments, the change interview will also be conducted by a researcher who did not have previous contact with the patient. With respect to follow-up measures, participants will be emailed (and reminded by telephone, if necessary) an individualized link to the questionnaires containing the same assessment protocol as in previous time points plus the CRES-4, for evaluating treatment satisfaction.

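### Giving questionnaire reminders to the blinded outcome assessors during therapy opens an avoidable route by which they can learn the arm before the post-treatment MINI

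*Protocol article*

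**What the plan says.** Four places in the protocol article bear on this.

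- **Reminders, {18b}:** "All patients will be reminded throughout the study to fill out the questionnaires by individualized emails as well as by therapists and outcome assessors". No form or period is excepted.
- **Blinding, {17a}:** "Researchers, patients, and therapists will not be blinded", but "researchers conducting outcome assessments will be blind to treatment allocation".
- **Data collection, {18a}:** during therapy, participants are emailed "individualized links to complete the CORE-SFB just before each session, and the SRS 3.0 for the therapeutic alliance" at its end. The post-treatment MINI is to be "performed, whenever possible, by the same evaluators who carried out the baseline interview". The change interview, by contrast, goes to a researcher with no earlier contact with the patient.
- **Schedule and use of the MINI:** Table 1 places the MINI at baseline and post-treatment only. The secondary outcomes section compares the percentage of remitted patients across arms on that interview.

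**The concern.** The BDI-II, CORE-OM, DASS-21, CRES-4 and life satisfaction scale are self-reports by patients who know their treatment. MINI remission is the between-arm efficacy comparison that rests on an interviewer's judgment, so it is where assessor blinding has most to protect.

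The reminder sentence gives those interviewers a reason to speak or write to patients while therapy is running. A prompt about a session form invites talk about the session. The SRS includes agreement with the method or approach, so a reply could easily mention a headset, a grid or CBT homework. An assessor who learns the arm this way may then make the remission rating. The plan avoids prior contact for the change interview but builds it in ahead of the MINI.

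**Working it through.** The document gives no figure for unblinding, so the check is mainly a reading of the sections in time order.

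1. **Before allocation.** The MINI evaluator sees the patient at baseline. Allocation follows the completed baseline assessments ({16b}, {16c}), so this contact cannot reveal the arm.
2. **During therapy.** Table 1 lists only the CORE-SFB and SRS, at every session. With at most 10 sessions before any boosters ({11a}), that is up to 2 × 10 = 20 forms per patient. Any questionnaire reminder between baseline and post-treatment that concerns a form then due therefore concerns a session form. {18b} names assessors among those who remind and does not limit them to other forms.
3. **Post-treatment.** Where possible the baseline evaluator repeats the MINI, and remission is compared across arms.
4. **Follow-up.** No MINI is scheduled, so reminders after the post-treatment interview cannot affect it. The exposure is confined to step 2.
5. **Safeguards described.** {17a} withholds the study hypotheses from patients and therapists. The article does not describe asking patients to keep their arm from assessors, or limiting what assessors may discuss. {18a} also allows forms to be filled in "even if participants are physically accompanied by their therapist or evaluators when completing the forms", which is a second occasion for contact.

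**Illustration only.** The unmasking and leaning rates below are assumptions with no source in the document.

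- Patients per arm: 75 less 5% dropout (Sample size {14}), 75 × 0.95 ≈ 71.
- Assumed true remission: 50% in both arms of a pair.
- Standard error of the difference: √(2 × 0.25 / 71) = 0.084.
- Spurious difference: share unmasked × lean in those patients.
- Two-sided false-positive rate: 1 − Φ(1.96 − shift/SE) + Φ(−1.96 − shift/SE). Two-sided is used because {20a} plans a chi-square test, which has no direction.

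| Share unmasked | Lean | Spurious difference | Shift/SE | False-positive rate |
|---|---|---|---|---|
| none | none | 0 | 0 | 0.05 |
| 30% | 15 points | 4.5 points | 0.54 | 0.08 |
| 50% | 20 points | 10 points | 1.19 | 0.22 |

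The table charges all unmasking to reminders and treats one pair of arms. It shows how the comparison would respond if assessors learned the arm and leaned. It does not show how often reminders would cause that.

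**The case against.** **The sections do not contradict each other.** A reader might infer that {18b} breaks the blinding promised in {17a}. It does not, because an assessor can send a reminder and remain blind. Nothing in the document says that a reminder discloses the arm or that assessors see allocation or session data. This stands, and it limits the point to a possible route.

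**The sentence may be a loose summary.** It names three channels without saying who prompts which form. Assessors may be meant to prompt only the baseline and post-treatment batteries. That is a fair reading, but the sentence as written does not make the restriction, and stating it is the remedy.

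**The MINI carries the risk anyway.** The post-treatment interview is held with a patient who knows the arm. True, but that is one contact, in which an interviewer can be prepared to deflect disclosure. Reminders during therapy add contacts that the rating does not need.

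**Therapist prompts and the BDI-II.** A reader might also infer that, because therapists are unblinded and work "in the therapy modality assigned", BDI-II completion will depend on arm. The document does not support this. The same channels serve all arms, links and reminders go out by email, the system alerts the team to uncompleted questionnaires, and the coordinator chases missing responses during follow-up. Uneven therapist effort is conceivable but nowhere stated, and dropping therapist prompts could itself lower completion.

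**Conclusion.** The point holds as a cheap improvement to protect blinding, not as an error that invalidates the analysis. The plan assigns assessors who must stay blind a task that brings them into contact with unblinded patients during therapy, and where possible the same people then rate remission. The route exists on the plain wording and is avoidable.

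Its size cannot be derived from the document. The rates of 0.08 and 0.22 rest wholly on assumed unmasking and leaning and should not be read as estimates. The primary outcome is not affected by this route, since the BDI-II is a self-report. No conclusion is drawn about BDI-II completion differing by arm.

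**What to change.** In {18b}, remove outcome assessors from the reminder duty until the patient's post-treatment MINI is complete. Until then, rely on the automated individualized emails already planned, with therapist prompts for the session forms. Add one sentence stating that MINI evaluators have no contact with a patient between the baseline and post-treatment interviews other than for scheduling, and align with it the remark in {18a} that evaluators may be present while forms are completed.

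Leave the coordinator's prompts in the follow-up period, after the last MINI, as planned. Moving the in-therapy prompts to the coordinator would not be a clean substitute: that person keeps the envelopes ({16c}), manages allocations ({5d}) and supervises the MINI diagnoses ({18a}).

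The cost is a small text change with no extra staff, visits or measures. One reminder channel is lost during therapy, which may slightly lower questionnaire completion.

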### Data management {19}

Data derived from questionnaires will be gathered through a secure web-based platform following security guidelines and policies and that has been approved by the university’s local ethical committee. The research team carrying out (outcome assessors) and supervising (trial coordinator) the assessment process and promoting data quality will undergo a 4-h training session on the data system and will count on the continuous supervision of principal investigators of the trial. Back-ups on the protected research server will be made regularly.

### Confidentiality {27}

With regard to the specific procedures to handle data, all researchers involved in its collection, custody, storage, and analysis within this trial will keep the strictest confidentiality about the personal information of participants. Likewise, the researchers who are part of the present project will commit themselves to not make any use of the personal data to which they may have access in the exercise of their assigned functions for any purpose unrelated to the project, as well as to neither share nor reveal that information to any third party. This obligation extends beyond the expiration of the research project and will be formalized by signing a confidentiality statement. The personal data collected in the context of the present research (recordings of the therapies, homework, etc.) will be stored securely in locked closets for both paper and digital (encrypted hard drive) formats. Only the principal investigator of the project may grant access to such files. For data analyses, anonymized databases will be used to further protect participants’ identities, assigning them an alphanumeric code. In any case, all the members of the trial will adjust to the provisions of the European law on the protection of personal data.

### Plans for collection, laboratory evaluation, and storage of biological specimens for genetic or molecular analysis in this trial/future use {33}

Not applicable since biological specimens are not collected for this trial.

## Statistical methods

### Statistical methods for primary and secondary outcomes {20a}

Intention-to-treat analyses (i.e., using outcomes from all randomized participants) will be performed for the main outcomes. Linear mixed models will be used to analyze and to compare treatment effects for the three treatment conditions (CBT, PCT, and PCT-VR). Baseline measurements, gender (coded as woman/male/not-binary), age, and clinical variables will be entered in the model as covariates. Pairwise comparisons will be used to test the hypothesis that PCT will lead to better outcomes than CBT and that PCT-VR will result in better outcomes than PCT. For all the analyses, effect sizes will be calculated.

In addition to the statistical significance, the proportion of patients who attain clinically significant improvement on the outcome measures will be calculated and compared between treatment conditions. The clinically significant improvement will be determined considering the proposal of Jacobson and Truax. For them, two conditions must be met: reliable change (reliability of pre-to-post difference in scores not being produced by chance) and clinically significant change (post-treatment scores lying in the normal instead of the clinical range). To test the differences in frequencies between the treatment conditions, a chi-square test will be applied.

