## Methods: participants, interventions, and outcomes

### Study setting {9}

This multi-center study will be conducted at several health facilities (primary care centers, tertiary hospitals, university clinics) in Barcelona and surrounding areas. Two mental health centers have confirmed their participation in the study (Hospital de Mataró and CSM Nou Barris). Due to COVID-19 restrictions and heavy workload, primary care centers that showed initial interest in participating in the study are not included at the time of writing this article. However, if restrictions change while the trial is carried out, these centers accepted the invitation to participate. An updated list of the participating centers will be updated in ClinicalTrials.gov.

Patients will be recruited at each health center and from an open call through social media. Patients are considered for inclusion if they meet the criteria defined below.

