## Assignment of interventions: allocation

### Sequence generation {16a}

Participants will be randomized to one of three arms in a 1:1:1 ratio, stratified by health center. Assignment will be conducted with computer-generated random block sizes of 3 or 6, masked from the study staff.

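### Randomisation is stratified by health centre, but the stated model covariates and the responder test leave centre out, so standard errors come out slightly too large

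*Protocol article*

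**What the plan says.** On randomisation, the Sequence generation section states: "Participants will be randomized to one of three arms in a 1:1:1 ratio, stratified by health center", using "computer-generated random block sizes of 3 or 6". Under Study setting, "Two mental health centers have confirmed their participation in the study", others may join later, and "Patients will be recruited at each health center and from an open call through social media". The protocol does not say to which stratum an open-call patient belongs.

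On analysis, the section on statistical methods for primary and secondary outcomes specifies linear mixed models and then lists the covariates: "Baseline measurements, gender (coded as woman/male/not-binary), age, and clinical variables will be entered in the model as covariates". Centre is not listed and no random effect is named. The same section compares the proportions with clinically significant improvement by a chi-square test, with no stratification.

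On therapists, the Intervention description says: "The three treatment modalities of the study will be applied by psychologists with specific clinical experience and training", and that this training is "in the therapy modality assigned". Therapy is individual. The Sample size section gives an effect size of 0.45, power 0.80, 5% dropout, one-sided alpha 0.1 and 75 patients per arm. It gives no allowance for clustering.

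**The concern.** Small blocks within centre force the arms to be nearly balanced in every centre. Differences between centres therefore hardly contribute to the true sampling error of the treatment contrast. An analysis without centre still leaves that variation in the residual, so it overstates the standard error and gives away some precision. The same holds for an unstratified chi-square test on responders. The list is explicit, down to the coding of gender, and the phrase about clinical variables cannot reasonably be read to mean centre.

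The open-call recruits matter because a stratum has to exist before a patient is randomised. A later analysis plan can decide how to model these patients, but it cannot decide retrospectively how they were randomised.

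Therapist clustering works in the other direction. Where each therapist treats in one modality only, patients of the same therapist may share part of their outcome, and that shared part does not cancel between arms. Ignoring it would make the standard error too small and the stated power too high.

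**Working it through.** **The plan's own figure.** The Sample size section states 225 patients, 75 per arm. With its inputs (0.45, power 0.80, one-sided 0.10), n = 2(1.2816 + 0.8416)²/0.45² = 44.5, so 45 per arm. Dividing by 0.95 gives 48 per arm, 144 in total. The figure of 75 appears if alpha is split in three (one-sided 0.1/3): 71 per arm, and 71/0.95 gives 75, or 225 in total. That mismatch is a separate matter, and this point does not rest on it. What matters here is that neither calculation contains a design effect, and that 75 per arm less 5% leaves about 71 evaluable (75 × 0.95 = 71.25).

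**Centre omitted.** Let ρ be the share of outcome variance lying between centres. The protocol gives no value, so 1% to 10% is assumed. With arms balanced within centre:

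- Unadjusted SE / correct SE = 1/√(1 − ρ)
- Actual one-sided level at nominal 0.10 = 1 − Φ(1.2816/√(1 − ρ))

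| ρ | SE ratio | Actual level |
|---|---|---|
| 0.01 | 1.005 | 0.099 |
| 0.02 | 1.010 | 0.098 |
| 0.05 | 1.026 | 0.094 |
| 0.10 | 1.054 | 0.088 |

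The error is conservative throughout.

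**Therapist ignored (conditional).** The protocol gives neither the number of therapists nor an intraclass correlation (ICC). Assume 3 to 12 therapists per arm (k), ICC 0.01 to 0.10, separate therapists in each arm, and 71 evaluable patients per arm. With caseload m = 71/k:

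- Design effect DE = 1 + (m − 1) × ICC
- True SE / unadjusted SE = √DE
- Actual level = 1 − Φ(1.2816/√DE)
- Power = Φ(0.45/√(2·DE/71) − 1.2816)

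| k per arm | ICC | DE | SE ratio | Actual level | Power |
|---|---|---|---|---|---|
| 12 | 0.01 | 1.05 | 1.02 | 0.105 | 0.91 |
| 5 | 0.05 | 1.66 | 1.29 | 0.160 | 0.79 |
| 3 | 0.10 | 3.27 | 1.81 | 0.239 | 0.58 |

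For the middle row, m = 14.2 and DE = 1 + 13.2 × 0.05 = 1.66. Without clustering, power at one-sided 0.10 with 71 per arm is 0.92. At ICC 0, DE = 1 and nothing changes.

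**Which contrasts this touches.** For CBT against either PCT arm, training by modality supports treating therapist as nested in arm. For PCT-VR against PCT, the protocol does not say whether the two arms share therapists, and the two therapy protocols differ only in the sessions where the grid results are visualised. If therapists are shared, therapist is crossed with arm in that contrast, and the table does not apply to it.

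**The case against.** The strongest reply is that this is a condensed article. It specifies mixed models and leaves the random part open, as is common before a statistical analysis plan. The quoted sentence lists covariates, which are fixed effects, so a missing therapist intercept there proves nothing. That stands. A reader might infer that the primary model leaves out the therapist and that its type I error therefore exceeds the stated level. The document does not support this: the term is neither stated nor excluded, the ICC is unknown, and the assumed range runs from negligible to severe. It would also be wrong to apply the design effect to PCT-VR versus PCT without knowing whether therapists are shared.

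The same reply has less force for centre. A random centre effect is not excluded either. But the fixed covariates are spelled out without the stratification factor, with only two confirmed centres a random effect is a poor way to carry it, and the chi-square test for responders has no place for it at all.

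A reader might also infer that open-call recruits fall in no stratum. That goes too far. The strata are health centres, not referring centres, and treatment is delivered in health centres, so these patients could be stratified by where they are treated. The gap is that the rule is not stated.

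Finally, the documented omission does not threaten the error rate. That is correct, and it limits the weight of the point.

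**Conclusion.** The stated analysis does not reflect the stated randomisation. Centre is missing from the covariate list and from the responder test, and the stratum for open-call patients is undefined. The cost is a modest loss of precision: standard errors about 0.5% to 5.4% too large if centre accounts for 1% to 10% of variance, which is an assumption because the protocol gives no figure.

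The therapist issue is secondary and conditional. It matters only if the therapist ICC is above zero and the analysis turns out to be unclustered. It applies to CBT versus the PCT arms, and to PCT-VR versus PCT only if therapists are not shared. Under the assumed ranges the true standard error would be 1.02 to 1.81 times the unadjusted one. The two effects have opposite signs, and neither can be relied on to offset the other.

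**What to change.** 1. Add health centre to the covariates of the primary model.
2. Replace the chi-square test on responders with a centre-stratified test such as Cochran-Mantel-Haenszel, or with a logistic model containing arm and centre.
3. State the stratum for open-call recruits, either the treating centre or a stratum of their own, and use the same definition in randomisation and analysis.
4. Record therapist identity for every patient and state whether PCT and PCT-VR share therapists. Specify a therapist random intercept with small-sample degrees of freedom (Kenward-Roger is one option).
5. Say in the Sample size section that the power assumes no therapist clustering, ideally with power under one assumed ICC.

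Items 1 to 3 cost only wording and one degree of freedom per additional stratum. Items 4 and 5 bring slightly wider intervals and a less favourable stated power. A random intercept carries therapist variation into the interval, but it cannot separate therapist from treatment where therapists work in one arm only, so the number of therapists per arm should be reported alongside the results.

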Thus, this project will allow us to test the hypothesis that VR-enhanced personal construct therapy (PCT-VR) will be more efficacious in the treatment of mild-to-moderate depression of young adults than PCT alone and the well-established CBT. We expect that PCT-VR, based on the immersive exploration of the patient’s self-identity, will make the treatment more attractive for young adults, increasing their engagement in the therapy process; therefore, our hypothesis is that PCT-VR will result in a greater reduction of depressive symptoms (primary outcome) and improve psychological functioning, well-being, and satisfaction, compared to psychotherapies delivered in the usual format. As a secondary hypothesis, we expect that PCT, thanks to its personalized and non-prescriptive nature, will be more efficacious than CBT. Also, as reflected in the literature, we expect that the quality of the therapeutic alliance will be associated to the outcome, but we will also explore whether this association varies in its intensity across therapy modalities.

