### Trial design {8}

This is a multi-center superiority randomized clinical trial, comparing the efficacy of two novel brief treatment modalities, PCT and PCT-VR, to CBT, a well-established treatment, with respect to their efficacy in treating young adults with mild-to-moderate depression. The comparison between PCT and PCT-VR will reveal the differential efficacy of including a VR app in the latter condition. The patient allocation ratio is 1:1:1.

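### The list of pairwise tests omits PCT-VR versus CBT, which is half of the main hypothesis, while naming the comparison declared secondary

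*Protocol article*

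**What the plan says.** All references are to the protocol article.

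- **Background and rationale {6a}**, main hypothesis: PCT-VR "will be more efficacious in the treatment of mild-to-moderate depression of young adults than PCT alone and the well-established CBT". The same paragraph identifies reduction of depressive symptoms as the primary outcome. This makes two contrasts: PCT-VR versus PCT and PCT-VR versus CBT.
- **Background and rationale {6a}**, next rank: "As a secondary hypothesis, we expect that PCT, thanks to its personalized and non-prescriptive nature, will be more efficacious than CBT".
- **Trial design {8}**: the trial is described as "comparing the efficacy of two novel brief treatment modalities, PCT and PCT-VR, to CBT". The Abstract (Background and Methods) and Objectives {7} also set PCT-VR against CBT.
- **Statistical methods for primary and secondary outcomes {20a}**, model: "Linear mixed models will be used to analyze and to compare treatment effects for the three treatment conditions (CBT, PCT, and PCT-VR)".
- **Same section**, purpose of the pairwise comparisons: "test the hypothesis that PCT will lead to better outcomes than CBT and that PCT-VR will result in better outcomes than PCT". No other pairwise test is named. The chi-square test for clinically significant improvement compares the conditions without naming contrasts.

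**The concern.** The analysis section does more than leave detail to a later plan. It lists its contrasts, and the list disagrees with the ranking of hypotheses in the Background. A contrast declared secondary is on the list; one of the two main contrasts is not.

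The missing contrast compares the new treatment with the reference standard. If the analysis section is followed as written, that claim has no test of its own. If the test is run anyway, readers can dispute whether it was one of the confirmatory comparisons, because the section that names the tests does not include it.

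A natural reply is that PCT above CBT and PCT-VR above PCT together imply PCT-VR above CBT. That is true of the underlying means. It does not follow that two significance tests will both succeed when the direct test would.

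**Working it through.** **1. Hypotheses against named tests**

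| Contrast | Rank in Background {6a} | Named as a pairwise test in {20a}? |
|---|---|---|
| PCT-VR vs PCT | main | yes |
| PCT-VR vs CBT | main | no |
| PCT vs CBT | secondary | yes |

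**2. The plan's own sample-size figure**

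Inputs from Sample size {14}: effect 0.45 (read here as a standardised mean difference), power 0.80, one-sided alpha 0.1, dropout 5%, giving 75 per arm and 225 in total.

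Formula: n per arm = 2(z₁₋α + z₀.₈₀)² / 0.45².

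- Alpha as stated: 2(1.2816 + 0.8416)² / 0.2025 = 44.5, so 45. Then 45/0.95 = 47.4, so 48 per arm and 144 in total. The stated 225 is not reproduced.
- Alpha split over three contrasts, 0.1/3 = 0.0333: 2(1.8339 + 0.8416)² / 0.2025 = 70.7, so 71. Then 71/0.95 = 74.7, so 75 per arm and 225 in total. The t-test version gives 76 per arm.

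The stated size therefore fits a design with all three pairwise tests. This is an inference from the match; the article does not mention a split.

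**3. Can the two named tests replace the missing one?**

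Evaluable patients: 75 × 0.95 = 71.25, taken as 71 per arm. Standard error of a difference in SD units: √(2/71) = 0.1678. One-sided 0.10 critical value: 1.2816. Power of one contrast with true difference d: Φ(d/0.1678 − 1.2816).

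- d = 0.45: Φ(2.681 − 1.282) = Φ(1.400) = 0.92
- d = 0.225: Φ(1.341 − 1.282) = Φ(0.059) = 0.52
- d = 0: 0.10

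The two named contrasts share the PCT arm with opposite sign, so their test statistics correlate at −0.5. A high PCT mean helps one test and hurts the other. The probability that both succeed is the bivariate normal probability with that correlation; simulation of the three arm means (1,000,000 runs) agrees.

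The article gives only the value 0.45. The arm patterns below are assumptions chosen to show the range.

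| Assumed effects, SD (CBT / PCT / PCT-VR) | Direct PCT-VR vs CBT | PCT vs CBT | PCT-VR vs PCT | Both named tests succeed |
|---|---|---|---|---|
| 0 / 0 / 0.45 | 0.92 | 0.10 | 0.92 | 7% |
| 0 / 0.45 / 0.45 | 0.92 | 0.92 | 0.10 | 7% |
| 0 / 0.225 / 0.45 | 0.92 | 0.52 | 0.52 | 19% |
| 0 / 0.45 / 0.90 | >0.99 | 0.92 | 0.92 | 84% |

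In the last row PCT-VR beats CBT by 0.90 SD, twice the planning effect.

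**4. Error across contrasts**

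With no true differences and each test at one-sided 0.10, the chance of at least one false positive is about 0.20 for the two named tests and about 0.235 for all three. Naming the third contrast therefore also calls for a statement on alpha.

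**The case against.** The strongest reply is that nothing has been dropped. The PCT-VR versus CBT comparison is announced in the Abstract, Background, Objectives and Trial design, with a direction and a primary outcome. The mixed model covers all three arms and can estimate it. The two named tests read like a ladder from CBT through PCT to PCT-VR, which suggests compressed drafting rather than a decision, and a fuller analysis plan may list every contrast.

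Most of this stands, and it limits the point. Three stronger readings that a reader might draw are not supported:

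- **That a later test of PCT-VR versus CBT would be post hoc.** A directional hypothesis published in the protocol is prespecified. What is unsettled is whether its test counts among the confirmatory ones.
- **That the plan spends a confirmatory test on a secondary hypothesis.** The section covers primary and secondary outcomes, labels neither comparison confirmatory and allocates no alpha. Testing PCT versus CBT there is proper.
- **That the loss has one fixed size.** It depends on where PCT lies, which the article does not say. The extreme case, in which the direct test is positive and both named tests miss, occurs in about 9% of trials in the midway pattern, about 3% if PCT equals CBT, and about 0.03% if each step is 0.45 SD.

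The reply does not remove the contradiction. An estimable contrast is not a named test, and an unseen plan that lists it would still conflict with this published list.

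**Conclusion.** The point holds as an internal contradiction. The analysis section names the secondary contrast and one main contrast, and omits the other main contrast, PCT-VR versus CBT. The omission is one of specification; the analysis remains possible with the planned model and data.

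The two named tests are not a dependable substitute. With PCT-VR better than CBT by 0.45 SD, the direct test has power of about 0.92, while both named tests succeed in 7% to 19% of trials across the patterns examined. The 84% figure needs each step to equal the full planning effect. These figures rest on 71 evaluable patients per arm, one-sided 0.10 without adjustment, a normal approximation with equal variances and no covariate gain, and assumed arm patterns.

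**What to change.** Reword the pairwise-comparison sentence in Statistical methods {20a} to match the Background:

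- primary contrasts on the BDI-II: PCT-VR versus PCT, and PCT-VR versus CBT;
- secondary contrast: PCT versus CBT;
- all three estimated from the same linear mixed model.

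Add one sentence on how the one-sided 0.1 in Sample size {14} applies across these contrasts, including whether both primary contrasts must succeed or either may, and whether alpha is split. If the sample size did rest on a three-way split, say so there.

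The cost is a wording amendment. Data collection, sample and model are unchanged. At 71 per arm and 0.45 SD, the added contrast has power of about 0.92 at one-sided 0.10 and about 0.80 at 0.10/3, so it needs no further patients under either reading.
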